#### Randomization

2.2.3

Participants (total *N* = 69) will be randomized into three different groups. After the baseline assessment and eligibility confirmation, the participants study identification sheet will be sent to an independent study team member responsible for the randomization. This study member will generate a list of random numbers using Researcher Randomizer.^1^ This list will define entry order into the randomization process and will allow proper allocation sequence concealment and prevent selection bias. Eligible participants will be randomized to: (*i*) moderate aerobic exercise training [AER: 60–70% HRmax; n = 23]; (*ii*) resistance exercise [RES: 8 exercises/major muscle groups; 8–15 reps; 60–70% 1RM; *n* = 23]; and, (*iii*) a combination of both [RES + AER; *n* = 23] groups at baseline. The randomization will be with a 1:1:1 allocation ratio since all groups are active interventions. The selection of this study design with all “active” groups reduces the possibility of potentially inferior treatment/no treatment and increases volunteers’ acceptability to recruitment. After the randomization, the study team will inform the exercise interventionist about the ID allocation. Due to exercise specificities blinding of participants and exercise instructors is not feasible. However, group allocation will only be communicated to participants immediately before the intervention. The exercise instructors will not perform outcome assessments nor data analysis, and the outcome assessors will be blinded to allocation groups. Participants will be informed to not reveal randomization groups during assessment visits.

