### Participant recruitment

2.2

Eligible volunteers will be recruited through an established collaboration with the community exercise program “*Mais e Melhores Anos*” at Famalicão. The inclusion criteria in our trial are based on the diagnosis criteria defined by the EWGSOP2 (27, 28) and thus, our goal is to enroll participants that have low skeletal muscle strength and quality. The assessment of eligibility will be made in two phases. In the first phase, prior to the screening visit, two members of the research team will analyze physical performance tests records collected in two different time points (October 2023 and June 2024), to identify eligible volunteers. Men and women who present handgrip test values below the sarcopenia cut-off point (men <27 kg and women <16 kg) will then be invited to an in-person screening visit to continue the eligibility assessment process. In this in-person assessment visit and prior to enrolment, − the second phase, each volunteer will receive a detailed explanation of all study phases and procedures, the benefits and risks along with all participant duties. Those that agreed to participate will provide their written informed consent as mandated by the Helsinki Declaration and its later amendments to protect human research (26). Afterwards, volunteers will be evaluated through additional complementary clinical and functional tests, including the assessment of body composition through dual-energy x ray absorptiometry, the Short Physical Performance Battery, the 4 meters gait speed, the 400 meters long distance corridor test, and through a handgrip dynamometry test—objective indicators of sarcopenia (27, 28), to confirm their eligibility. Those who met all the inclusion/exclusion criteria will be randomly assigned to one of three different exercise training interventions: (i) aerobic exercise (AER) training; (ii) resistance exercise (RES); or (iii) concurrent training (RES + AER).

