### Assessments

2.5

Participants will be evaluated in three different moments: (i) baseline; (ii) end of the intervention (12 weeks); (iii) close-out (24 weeks). The study has a total duration of 26 weeks. In each study visit, participants will perform the same physical and functional assessments, body composition analysis, and provide a fasting blood and feces sample. Other confounding variables will also be recorded, including nutritional intake (through a 3-day diary), daily PA levels (through a PA tracker), medication intake. Medication and supplementation along with other associated comorbidities will be assessed using a medical questionnaire and medication history questionnaire. Considering the study design, the following outcomes will also be evaluated: (a) retention and attrition rates; (b) adherence to exercise intervention; (c) safety; (d) intervention effect on dependent outcomes (Table 4).

**Table 4 tab4:** Overview of the assessment visits and data collection at each visit.

Study phase	Pre-randomization		Intervention		Follow-up
Visit description	Screening	Baseline	Start	End	CO
Visit number	1	2	3	4	5
Week number	−2	0	2	14	26
Informed consent, review inclusion/exclusion criteria	x				
Demographic information, medical history, medication use	x				
IPAQ questionnaire	x				
Office blood pressure	x	x	x	x	x
Anthropometry measurements	x	x		x	x
Randomization	x				
Body composition (DEXA)		x		x	x
Blood and fecal samples for study assays		x		x	x
Nutritional Intake		x		x	x
Skeletal muscle strength		x		x	x
Physical performance testing		x		x	x
Daily physical activity		x	x	x	x
Assess adverse events			x	x	x
Exercise intervention			x	x	

CO, close-out.

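### Table 4 marks randomisation at Screening, before the DXA that settles eligibility, against sections 2.2 and 2.2.3 and the table's own header

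*Protocol article*

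**What the plan says.** Two places in the text give the order of events. Section 2.2.3 (Randomization) states: "After the baseline assessment and eligibility confirmation, the participants study identification sheet will be sent to an independent study team member", who generates the random list. Section 2.2 (Participant recruitment) describes an in-person screening visit with tests that include "the assessment of body composition through dual-energy x ray absorptiometry, the Short Physical Performance Battery, the 4 meters gait speed", done to confirm eligibility, and then says: "Those who met all the inclusion/exclusion criteria will be randomly assigned to one of three different exercise training interventions".

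Table 4 in section 2.5, titled "Overview of the assessment visits and data collection at each visit", has five visit columns: Screening (week -2), Baseline (week 0), Start (week 2), End (week 14) and close-out (week 26). A phase header above the first two calls both of them pre-randomisation. The randomisation row has a single mark, under Screening. Body composition by DXA, skeletal muscle strength, physical performance, and blood and stool samples are all first marked at Baseline.

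The row "Demographic information, medical history, medication use" is also marked at Screening only. The text of section 2.5 lists medication intake, with diet and daily activity, among the confounders to be recorded, and refers to a medication history questionnaire that also covers supplements.

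**The concern.** Section 2.2.1 requires low handgrip strength together with a low appendicular skeletal muscle index. The protocol obtains body composition by DXA, so a person's muscle-index status is unknown until the scan is done. A schedule that allocates at week -2 and scans at week 0 allocates people before one of the two defining inclusion criteria can be checked.

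Section 2.6 commits the primary analysis to intention to treat. Anyone who then failed the muscle index would either stay in the analysis without meeting the definition of sarcopenia that the trial uses, or be removed after randomisation. The first dilutes the target population; the second departs from the stated principle. Site staff often work from the visit table, so the mark could have practical effect.

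The medication row raises a similar but smaller point. The Introduction names medication and supplement use as sources of variation in the microbiome, and the primary outcome is a microbiome measure. The table schedules no record of either after Screening.

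**Working it through.** The protocol states no figure on this point that could be reproduced. The check consists of reading Table 4 column by column and setting it beside the text.

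| Item | Text | Table 4 |
|---|---|---|
| Randomisation | After baseline assessment and confirmed eligibility (2.2.3); only for those meeting all criteria (2.2) | Screening, visit 1, week -2 |
| Phase label | – | Screening and Baseline both before randomisation |
| Eligibility DXA | In-person screening visit (2.2) | First at Baseline, visit 2, week 0 |
| Strength and physical performance tests | In-person screening visit (2.2) | First at Baseline, week 0 |
| Stool sample (primary outcome) | Each of the three assessment visits (2.5) | Baseline, End, close-out |
| Medication use | Among the recorded confounders (2.5) | Screening only |

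**Order of events.** Week of first DXA minus week of randomisation = 0 − (−2) = 2 weeks, with randomisation first. Sections 2.2 and 2.2.3 give the reverse order.

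**Is the mark a reading error?** The randomisation row is laid out like the consent, demographics and IPAQ rows, which plainly belong to Screening. An extraction fault is therefore unlikely, though it cannot be excluded.

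**Which criteria are open at week -2?** Handgrip is pre-screened from records of October 2023 and June 2024, and only people below the cut-off are invited. Section 2.2.1 presents gait speed and SPPB as measures of severity, although section 2.2 lists them among the confirming tests. The muscle index is the criterion that is clearly unknown.

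**Would moving the mark be enough?** No. With the mark after Baseline, section 2.2 would still place the eligibility DXA and functional tests at the screening visit while the table places them at Baseline. Either can work, provided the scan precedes allocation, but the two passages must name the same visit.

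**Is there room in the calendar?** Baseline is at week 0 and the intervention starts at week 2, which leaves 2 − 0 = 2 weeks for allocation.

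**Medication.** In the section 2.5 list, diet and daily activity stand beside medication. Table 4 marks both of those at Baseline, End and close-out (activity also at Start). Medication is the only one of the three without later marks.

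**The case against.** The strongest reply is that this is one misplaced mark. Sections 2.2 and 2.2.3 and the table's phase header all put randomisation after eligibility, and one cell disagrees. That is probably right. A reader might infer from the table that the trial intends to randomise before eligibility is known; the documents do not support that. What stands is that an operational table contradicts the text, and that the visit for the eligibility DXA differs between section 2.2 and Table 4 wherever the mark goes.

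A reader might also infer that baseline stool samples, diet logs and effort-dependent tests would be biased because they follow allocation in an open-label trial. Section 2.2.3 answers most of this: participants learn their group only just before training begins, and outcome assessors are blinded. Bias in baseline measures is therefore a lesser concern. Those safeguards do not help with allocating people whose eligibility is unknown.

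On medication, a reader might conclude that antibiotic or probiotic use during the trial would go unrecorded. That follows only if the table overrides the text. Section 2.5 describes what happens at each study visit and then lists medication among the confounders, so repeated recording is the more natural reading. What remains is a text-table mismatch.

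**Conclusion.** The inconsistency is real and should be corrected before the schedule is used. Table 4 puts randomisation two weeks before the first DXA, the text puts it after eligibility is confirmed, and section 2.2 and the table disagree on which visit supplies the eligibility tests. It is most likely a drafting slip, so this is a moderate point about internal consistency and not evidence of a flawed design.

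The harm is conditional on the printed table being followed. In that case, ineligible people would enter the intention-to-treat set or be excluded after randomisation. It is tempting to put a number on this, but the documents give no rate at which volunteers with low handgrip fail the muscle index, so any count would rest on an invented rate. The sample size calculation is not affected.

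The medication row is a secondary mismatch of the same kind.

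**What to change.** 1. In Table 4, move the randomisation mark to a point after all Baseline (week 0) procedures and before visit 3 (week 2). This matches section 2.2.3 and the table's header.
2. Make section 2.2 and Table 4 name the same pre-randomisation visit for the eligibility DXA and functional tests. Either mark them at Screening in the table, or state in section 2.2 that the Baseline values decide eligibility and precede allocation. If they are marked at both visits, participants are tested twice. If only at Baseline, some people will complete baseline procedures and then prove ineligible.
3. Mark medication and supplement use at weeks 0, 14 and 26, using the questionnaire already planned.

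The first two are corrections to the table and one sentence, with no change to the sample size or the three-arm design. The third costs a few minutes at each visit.

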#### Inclusion/exclusion criteria

2.2.1

Participants will be included if: (*a*) aged ≥60 years; (*b*) present objective indicators of sarcopenia recommended by the EWGSOP2 [handgrip strength: men <27 kg and women <16 kg + appendicular skeletal muscle index/ height^2^: men <7.0 kg/m^2^ and women <5.5 kg/m^2^; severity will be assessed by the 4-m gait speed ≤0.8 m/s; SPPB ≤8-point score; Chair stand test >15 s; Time-up-go ≥20 s]; (*c*) level of PA ≤150 min/week of moderate PA assessed using the International Physical Activity Questionnaire (IPAQ)- Portuguese version (29); (*d*) Willingness to participate in all study procedures regardless of possible group allocation. In contrast, participants will be excluded if: (a) fail to provide consent; (b) present uncontrolled hypertension: (c) Systolic Blood Pressure (SBP) > 180 mmHg or Diastolic Blood Pressure (DBP) > 110 mmHg; (d) history of coronary artery stenosis (>50%); (e) heart failure: ejection fraction <50%; (f) history of syncope at exertion; (g) history of hypertrophic cardiomyopathy; arrhythmogenic cardiomyopathy, dilated cardiomyopathy or evidence in the previous 6 months of myocarditis or pericarditis; (h) severe valvular heart disease; (i) chronic kidney disease stage ≥4.8; (j) chronic obstructive pulmonary disease stage ≥3.9; (k) musculoskeletal or neurodegenerative conditions that hinders exercise engagement; (l) current participation in another structured exercise training program; (m) inability to commit to study procedures or the exercise intervention throughout the study period; (n) other condition or concern precluding safe participation.

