#### Sample size

2.2.2

The sample size was calculated based on a previous study (3) were authors saw a large effect after the intervention (Cohen d’s effect size = 1.15). Given that to date, there are no consensus in the optimal method to analyze microbiome health status, we selected the change on the relative abundance of *Faecalibacterium prausnitzii* and other SCFA (Short-Chain Fatty Acid) producing bacteria after the intervention (12-weeks) as our primary outcome. Nonetheless, this pilot study was powered to detect a more conservative effect size- of 0.9 on *Faecalibacterium prausnitzii* relative abundance after the intervention between experimental groups. Assuming an 80% power, a two-sided significance level of 0.05, we would need a total of 21 participants/group (calculated on GPower version 3.2). With an allocation ratio of 1:1:1 and an attrition rate of 10%, the final sample is of *N* = 69 (*n* = 23/group) participants.

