#### Skeletal muscle function

2.5.2

Dominant lower limb knee extension and flexion muscle strength will be assessed through an isokinetic dynamometer, the Biodex System 3 Pro isokinetic dynamometer (System 4 Pro™, Biodex Medical Systems, Shirley, New York, United States) at baseline, end of intervention and close-out. The isokinetic dynamometer is the gold standard method for muscle strength assessment, allowing precise evaluation of force generation within a pre-established range of motion and speed. Test parameters will be defined according to the manufacturer instructions, namely: 90° dynamometer orientation, 0° tilt, 90° seat orientation, 80° seatback tilt and axis of rotation aligned with the lateral femoral condyle determined by inspection and palpation. Participants will be asked to avoid strenuous physical activities in the 48 h prior to testing. Participants will complete a 1 min warm-up consisting of leg extensions and flexions without load while seating in the equipment chair. Afterwards, participants will be fixed to the equipment chair with straps and a passive knee flexion starting from 0° extension will be performed to assess leg weight for gravity correction purposes. Participants will then perform two training sets of 5 reps of isokinetic extension/ flexion at 60°/s, between 0 and 90° range, with a 30s rest interval between sets. After 2 min rest, patients will perform two testing sets of 5 reps with 90s rest interval between sets. Patients will perform the test by exerting maximum possible pressure on the isokinetic arm throughout the entire range of movement. Standardized instructions will be given to encourage maximal muscle performance throughout the test. Peak torque of extension and flexion total work (J) obtained throughout the test in each valid set will be recorded. Maximal muscle strength will be defined as the highest peak torque (Nm) obtained. To avoid sub-maximal performance or outliers, if the peak torque coefficient of variation between the 3 best testing sets exceeds 15%, a new testing set will be performed until a lower than 15% coefficient of variation is obtained between 3 sets. Non-dominant handgrip strength will be assessed using a hand dynamometer (Jamar Plus+ Digital Hand Dynamometer) with participants seated, shoulder adducted in neutral rotation, arm at the side of the body and elbow flexed at 90°. Participants will be encouraged to exert their maximum grip strength. Three repetitions of 3 s will be performed with 30 s interval. The average value of the two repetitions with the lowest coefficient of variation will be considered.

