
#### Anthropometry and body composition

2.5.3

Body weight (BW) and height will be measured using a precision scale coupled to a stadiometer (Seca 285). The Body Mass Index (BMI) will be calculated using the BMI = weight/height^2^ equation. Waist and hip circumferences will be measured with a measuring tape (Seca 203) according to WHO guidelines (33), and then waist-to-hip and waist-to-height ratios will be calculated. Body composition and percentage body mass will be assessed by whole-body DXA (DXA; Hologic Explorer QDR) according to the manufacturer recommendations and using standard protocols for positioning and analysis of the DXA scans. The same DXA equipment will be used throughout the experimental period. All scans will be performed and analyzed by the same trained researcher. Phantoms will be scanned daily, and coefficients of variation will be analyzed during the experimental period to ensure reliability. In every assessment (baseline, end of the intervention, and close-out) each participant will perform a whole-body scan for total and regional body composition. The outcome variables obtained with DXA are total and regional lean mass (kg, %), total and regional fat mass (kg, %), absolute appendicular skeletal muscle mass, relative appendicular skeletal muscle mass per weight, height and BMI. All participants will be assessed between 8 and 10 am following a > 8 h fasting period while wearing only light cloths. For whole-body composition assessment, participants will lie supine with arms alongside, legs in extension and slight internal rotation with feet attached by a Velcro strap. Anthropometric measurements and body composition will be assessed using appropriate procedures and gold standard methods.

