### Statistical analysis

2.6

Descriptive and exploratory analyses will be performed, and normality will be assessed using the Kolmogorov–Smirnov or Shapiro–Wilk tests, and if necessary, the data will be transformed for normalization. The differences between the baseline groups will be explored using one-way analysis of variance (ANOVA) or Kruskal-Wallis tests for continuous data and chi-square tests for categorical data.

The intention-to-treat principle will be used for the primary outcome analysis. The main analyses will employ random coefficient linear mixed models for normally distributed endpoints or generalized mixed models for non-normally distributed endpoints. Post-hoc analysis with Bonferroni correction will assess differences between treatment factors. Cohen’s d will be used to indicate the effect size, and significance will be set at *p* < 0.05.

Fecal samples will undergo taxonomic analysis, grouped into amplicon sequence variants (ASVs), and summarized at different taxonomic levels. These data will be imported in R for use with the Phyloseq package. Several indices of alpha and beta diversity will be evaluated (i.e., Simpson Index, Shannon-Wiener Index, Bray–Curtis dissimilarity, Unweighted and weighted Uni-Frac for beta-diversity). Principal Coordinate Analysis (PCoA) will be performed to visualize the dissimilarity matrix between all samples and a PERMANOVA on exercise groups will be performed. Analysis of Compositions of Microbiomes (ANCOM) with bias correction will be used to test for differential abundance of individual ASVs at several levels to compare the three exercise groups. We will use the Benjamin– Hochberg corrected significance level of 0.05 to minimize false discovery rate (FDR). For the metabolomics analysis, samples will be normalized by the total ion current and means centered using Pareto scaling. Univariate analysis of variance will be performed on data from both ion modes to identify variations in peak areas between groups at baseline and after the 12-weeks intervention. Partial least squares discriminant analysis (PLS-DA) will be used to detect the most critical discriminant metabolites in each comparison across groups consistent with published guidelines for metabolomics trials (36). Microsoft packages (e.g., Excell), SPSS (version 27) and R (version 4.2.) software will be used to manage and analyze the different data.

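### The allocation list is not stratified by sex although the grip and muscle-index entry limits are sex-specific: at 23 per arm this leaves avoidable chance imbalance, a minor cost in precision and not a bias

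*Protocol article*

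**What the plan says.** Section 2.2.3 (Randomization) describes how the list is made: "This study member will generate a list of random numbers using Researcher Randomizer". Allocation is 1:1:1 with 23 per arm. The section mentions no stratification factor, block or minimisation.

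Sex matters at entry. Section 2.2.1 sets "handgrip strength: men <27 kg and women <16 kg" and an appendicular muscle index below 7.0 kg/m² for men and 5.5 kg/m² for women. Sex must therefore be known before anyone is allocated.

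Several outcomes are then taken in absolute units. Section 2.5.2 states: "Maximal muscle strength will be defined as the highest peak torque (Nm) obtained", and handgrip is measured as well. Section 2.5.3 lists lean mass in kg, but also in percent, and appendicular mass relative to weight, height and BMI.

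Section 2.6 states: "The main analyses will employ random coefficient linear mixed models for normally distributed endpoints", with generalised mixed models for other endpoints. It lists no covariates. The only one explicitly assigned to a model is daily physical activity, for the primary outcome (section 2.3).

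**The concern.** The protocol treats sex as important enough to set separate entry limits and then gives it no role in allocation. The women's limit is 41% below the men's for grip ((27 − 16)/27) and 21% below for muscle index ((7.0 − 5.5)/7.0). With three arms of 23, an unrestricted list can leave the arms with visibly different sex mixes. The hypotheses at the end of section 2.6 include greater muscle mass, strength and physical performance with concurrent training. A chance surplus of men in one arm could make those comparisons harder to read, and variation due to sex that the model does not absorb costs precision.

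Stratification has to be settled before the first allocation, so a later analysis plan cannot supply it.

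**Working it through.** **1. The plan's own sample size.** Inputs from section 2.2.2: "Assuming an 80% power, a two-sided significance level of 0.05", d = 0.9. A two-sample t-test needs 20.39 per group, rounded up to 21, where power is 81.2%. Attrition: 21 × 1.1 = 23.1, so 23 per group and 69 in total. The stated figures reproduce.

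**2. How much imbalance to expect.** Allocate 69 people at random to 3 × 23, with F women among them (multivariate hypergeometric, 200,000 draws). The protocol gives no sex mix, so 50% to 80% women is assumed. For two given arms, the SD of the gap in the proportion of women is √[(2/23) × p(1 − p) × 69/68]. For F = 34 this is 0.149, against 0.148 simulated. Gaps of 3 and 5 women are 13 and 22 percentage points.

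| Women (F) | SD of gap, given pair | Given pair ≥5 women | Some pair ≥5 women | Some pair ≥3 women | Mean largest gap |
|---|---|---|---|---|---|
| 50% (34) | 14.8 points | 19% | 38% | 76% | 18 points |
| 60% (41) | 14.6 | 18% | 36% | 75% | 17 |
| 70% (48) | 13.6 | 15% | 34% | 68% | 16 |
| 80% (55) | 11.9 | 10% | 22% | 65% | 14 |

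**3. Effect of a sex difference in level only.** Simulated two-arm comparison, 23 per arm, 70% women, 4,000 runs. Assumed: sex gap in level of 2 within-sex SD, pre-post correlation 0.8, realised imbalance 4/23.
- Raw follow-up level: shift = 2 × 4/23 = 0.35 SD (simulated 0.35).
- Change from baseline: 0.00.
- Baseline-adjusted: 0.04 SD.

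**4. Effect of a sex difference in response.** Let h be the sex difference in change, in within-sex SD (assumed 0.3 to 0.5). The shift in a change contrast is h × gap.
- h = 0.3: 0.3 × 5/23 = 0.065.
- h = 0.5: 0.5 × 5/23 = 0.109.
- In overall SD units, divide by √v with v = 1 + p(1 − p)h². At p = 0.5, v is 1.0225 and 1.0625, giving 0.064 and 0.105.

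So the shift is about 0.06 to 0.11 SD. The simulation with h = 0.3 and a 4/23 gap gave 0.05 for change and 0.07 baseline-adjusted.

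**5. Precision and power.** Under random allocation, adding sex to a baseline-adjusted model lowered the standard error from 0.183 to 0.180 SD when both sexes change equally, and from 0.190 to 0.177 when men change by 0.3 SD more. For power at n = 21, adjusting for sex raises the effective d to 0.9 × √v.
- h = 0.3: d = 0.910, power 82.1%.
- h = 0.5: d = 0.928, power 83.5%.

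Against 81.2%, the gain is about 1 to 2 points. This is illustrative only, because the 0.9 was set for the bacterial outcome.

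**6. Error rate.** Over repeated random allocation the mean shift was 0, and type I error was 4% to 5% in every analysis, with or without sex.

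**The case against.** The strongest reply is that this is a preference and not an error. The article condenses a fuller protocol, and no analysis plan is shown. Section 2.6 gives no covariate list, so the absence of a sex term is not a finding in itself. That stands; the point rests on the described list, with the sex term as its companion.

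Three stronger readings are tempting, and the documents do not support them.

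- **That the imbalance biases the comparison and nothing in the plan corrects it.** Imbalance from random allocation is not bias. Baseline and two later visits are planned with mixed models, so a constant sex difference in level cancels from the arm-by-time contrast (step 3).
- **That a 5/23 gap moves mean handgrip by 11 kg × 5/23 = 2.4 kg.** This concerns raw levels only, and the 11 kg is the distance between two upper entry limits, not between the sexes' means.
- **That adjustment would raise power well above the planned level.** Reaching 94% would need a sex difference in change of about 1.5 SD. No section gives any sex difference in response, and the entry limits speak to level only. The 0.9 SD also belongs to *Faecalibacterium prausnitzii*, with no stated link to sex.

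It is also true that strength and body composition are complementary outcomes (section 2.4.2), that lean mass is also expressed in relative units, and that the entry thresholds for gait speed, SPPB and chair stand are the same for both sexes.

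The reply does not remove everything. Some planned comparisons are worded on levels after the intervention: the null hypotheses in section 2.6, and the metabolomics analysis of variance, which compares peak areas between groups at baseline and after 12 weeks. Cancellation does not apply if those are run as written. How far sex affects taxa or metabolites is not given.

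**Conclusion.** The point holds as a minor design improvement. Some sex imbalance is probable (65% to 76% for a gap of at least 3 women between some pair of arms). A gap of at least 5 is plausible but less likely than not (22% to 38%), and for any one named pair it is 10% to 19%.

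The consequence is small: slightly lower precision and, in the one trial that is run, a conditional shift of about 0.06 to 0.11 SD for a 5/23 gap if the sexes differ by 0.3 to 0.5 SD in change. A comparison of raw follow-up levels would be more exposed. The sex mix, the 2 SD level gap, the 0.8 correlation and the response differences are all assumptions. No stated figure in the protocol is wrong on this account.

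**What to change.** Have the independent team member generate the list in permuted blocks of concealed, varying size within two strata, men and women. Include sex as a fixed effect in the between-arm models. If allocation has already begun, leave the list alone and pre-specify the sex term before the data are analysed.

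The cost is a few lines in the list generation and one degree of freedom per model. No new data are needed, because sex is already required to apply the entry limits, and the sample size stays at 23 per arm.
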